## Methods

### Overview of study design

An open-label, parallel-group design study will be used to investigate whether a higher RS intake from diagnosis of GDM changes the gut microbiome and improves glycaemic control compared with standard dietary advice. Educating women to consume a diet consistent with evidence-based recommendations for the dietary management of GDM [40] was chosen as the comparator group as it is safe for participants and this study aims to evaluate whether the interventions are more effective than usual care.

Participants will enter the trial at diagnosis with GDM between 24 and 30 weeks of gestation. Informed written consent will be obtained by the Principal Investigator (PI) prior to randomisation into one of three dietary treatment groups – standard dietary treatment for GDM (Control), a high RS diet (RS Diet) or a high RS diet plus an RS supplement (RS Supp). The dietary intervention will continue until delivery. Measurements will be taken at Baseline over Days 1–3 (where they will be between 24 to 36-weeks’ gestation), Day 10, Day 56 (approximately 36-weeks’ gestation) and 1-week after delivery (Fig. 1).

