### Sample size

In a study by Asemi et al. [42], the average woman with GDM has a mean FBG of 5.175 ± 0.86 mmol/L. In RS supplementation trials, a difference in FBG as large as 0.4 mmol/L has been observed between control and RS supplemented groups [38]. This study aims to demonstrate a reduction in FBG of 0.3 mmol/L, which corresponds to a small to medium Cohen’s effect size (*d* = 0.35). Based on a repeated-measures design with three groups (Control, RS Diet, RS Supp) and three time points (Baseline, Day 10 and approximately Day 56), a minimum sample size of 69 (i.e., 23 per group) is required to detect a small to medium within-between interaction effect (Cohen’s *f* = 0.175) at 80% power and 5% level of significance. Allowing for an attrition rate of around 30%, the final total sample size required is 90 (i.e., 30 per group). Women who commence insulin therapy will remain in the study.

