### Primary outcome

#### Fasting blood glucose

The primary outcome of this study will be a reduction in median FBG from Baseline, within and between groups. Baseline FBG will be recorded from the diagnostic OGTT results [41]. Subsequent venous blood samples will be collected after an overnight fast at Day 10 and Day 56 and analysed for FBG following protocols from the National Association of Testing Laboratories. FBG within treatment targets (< 5.1 mmol/L) [49] is the measure of glycaemic control that has been most difficult to achieve with standard GDM diet and lifestyle interventions and therefore the variable most likely to indicate the need for medical therapy, such as insulin [50]. If FBGL below 5.1 mmol/L is not achieved by Day 10, insulin therapy will commence. Participants treated with insulin will remain in the study.

Routinely women will receive self-monitoring of blood glucose (SMBG) education. Participants will be provided with an SMBG meter and instructed on measuring blood glucose levels four times daily (FBG and 2-h post-prandially). The SMBG meters used will be either Contour Next (Ascensia Diabetes Care, Switzerland), Accu-Chek Guide (Roche Diabetes Care, Switzerland) or One Touch Verio (LifeScan, USA) and meet International Organization for Standardization (ISO) standards for accuracy. Data from these models will be uploaded via the Diasend Uploader (Glooko, USA). FBG will be monitored on the first 2 days and averaged to provide a Baseline measure. This will be compared to the moving averages over the subsequent 8 days of testing, and then again between Days 48 and 56, across the three dietary groups (Control, RS Diet and RS Supp) using mixed model ANOVA with group-by-time interaction.

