### Statistical analyses

Baseline demographic and outcome variables will be described and compared for differences between groups. Continuous variables will be described as mean ± standard deviation (SD) and nominal and ordinal variables as frequencies and proportions. All continuous variables will be examined for normality using the Shapiro-Wilk test. Descriptive statistics for non-normal continuous variables will be presented as median ± interquartile range (IQR).

FBG and PPBG will be monitored on the first 2 days and averaged to provide a Baseline measure of each outcome. These will be compared to those measured over the subsequent 8 days, and then again between Days 48 and 56, across the three dietary groups (Control, RS Diet and RS Supp) using linear mixed modelling with group-by-time interaction. Analysis will assess if a 0.3 mmol/L reduction is achieved. Demographic variables such as age, pre-pregnancy BMI, parity and ethnicity will be adjusted in the model. Statistical analyses will be performed using SPSS® (Statistical Package for Social Sciences, version 27 for Windows).

The number of PPBG excursions experienced by a participant per day between Days 4 to 10 will be examined and compared relative to the number determined at their Baseline over the first 2 days of the usual care diet. Generalised Mixed Modelling will be utilised to assess whether a dietary change reduces the frequency of PPBG excursions as compared with norm with adjustments for relevant demographic variables.

Different R packages and PRIMER 7 (Quest Research, NZ), a non-parametric statistical software package, will be used to assess change within and between groups for microbial composition. Distance Based Linear Modelling (DistLM) will be used to look for a correlation between change in stool microbiota or SCFA & measures of glycaemia.

Direct and indirect costs savings related to any reduction in insulin treatment or improvements in maternal and neonatal outcomes will be calculated from DRG codes, Weighted Activity Units (WAU) and the National Efficient Price (NEP) and reported [74].

Missing data will be treated in statistical analysis as missing and coded as 999 or left blank, so as not to affect the accuracy of the analysis. Prior to any statistical analysis, all data will be explored for outliers. Any outliers found will be cross-checked with the source file. Any true outliers will be checked with the clinician before being removed/left in the dataset.

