Studies have characterised gut microbiome changes in the GDM population [21, 22, 35, 78, 79], assessed the effect of dietary manipulations on the maternal gut microbiome [35, 80, 81] or the relationship between the microbiome and glycaemic control in GDM [22, 23, 78, 79, 82]. However, very few randomised control trials have examined all these parameters in the same study, using a diet intervention to manipulate the gut microbiome to improve glycaemia and achieve better outcomes in a GDM population. For instance, Mokkala et al. [81] showed that fish oil and probiotic supplements were not effective in altering the microbiome or serum glucose in overweight and obese GDM women. To our knowledge, there are no studies that have investigated the relationship between dietary RS intake, the gut microbiome, glycaemic control and maternal and foetal outcomes in pregnancies affected by GDM, therefore, this needs to be explored as a lifestyle and economical approach to management.

This open-label, parallel-group design study will build on the emerging relationship between dietary RS, the gut microbiome and improved blood glucose levels [24–28]. It will not only characterise the changes to the maternal gut microbiota in response to a higher dietary intake of RS but proceed to identify any correlation between these microbial changes and improvements in glycaemic control. Again, only a few studies have done this in non-pregnant populations. Additionally, it will investigate whether maternal microbial changes in response to RS can alter the microbiota of the neonate, possibly inoculating the next generation with a more favourable microbiota. Also unique to this study is the assessment of whether a high dietary intake of RS from whole foods alone can improve glycaemic control in GDM, or if an RS supplement is required to achieve a positive result.

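### The primary outcome allows a within-group fall in fasting glucose to count and names no arm, visit or reference, so a fall unrelated to resistant starch could meet it

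*Protocol article*

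**What the plan says.** The Overview of study design sets out the arms as follows: "standard dietary treatment for GDM (Control), a high RS diet (RS Diet) or a high RS diet plus an RS supplement (RS Supp"). Under Primary outcome, the section on fasting blood glucose (FBG) reads: "The primary outcome of this study will be a reduction in median FBG from Baseline, within and between groups". The Baseline value is the FBG from the diagnostic glucose tolerance test, and "Subsequent venous blood samples will be collected after an overnight fast at Day 10 and Day 56".

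The analysis is named in two places. The primary outcome section compares FBG "across the three dietary groups (Control, RS Diet and RS Supp) using mixed model ANOVA with group-by-time interaction", and Statistical analyses does so "using linear mixed modelling with group-by-time interaction". Both sentences describe averages of self-monitored values. Statistical analyses then adds: "Analysis will assess if a 0.3 mmol/L reduction is achieved". It does not say in which arm, at which visit, or against what.

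The Sample size section attaches the error rate to the interaction alone: 69 women "is required to detect a small to medium within-between interaction effect (Cohen’s *f* = 0.175) at 80% power and 5% level of significance". The Discussion says the trial will assess whether eating RS only in the form of whole food "can improve glycaemic control in GDM, or if an RS supplement is required to achieve a positive result".

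**The concern.** The primary outcome sentence covers two kinds of comparison (change within an arm, difference between arms), two RS arms and two visits, and nothing in the article ranks them. The interaction test is a single omnibus test with 4 degrees of freedom. A significant result says that the three time profiles are not parallel. It does not say whether RS Diet or RS Supp departs from Control, at which visit, or whether glucose fell or rose. The Discussion's question about whole foods or supplement therefore needs arm-specific contrasts whose status is not fixed.

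The within-group reading matters most because falls unrelated to RS are plausible in every arm:

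- All women receive standard dietary advice for gestational diabetes.
- Baseline is the diagnostic value, and a raised fasting value is one route into the trial, so some regression to the mean is expected.
- Women who start insulin under the Day 10 rule stay in the study.

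Any of these can lower FBG in an RS arm with no effect of RS. As worded, such a fall meets part of the primary outcome, and the reading that decides the trial could be chosen after the data are seen.

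**Working it through.** **Inputs from the article.** Three arms; Baseline, Day 10 and Day 56; SD 0.86 mmol/L; target 0.3 mmol/L; f = 0.175; 5% level; 80% power; 23 per arm evaluable, 30 per arm randomised.

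**Assumptions.** The correlation ρ between visits is not stated. It is taken as 0.5 and varied from 0.3 to 0.7 where noted. Tests are two-sided, because the article gives no sidedness. The common fall of 0.3 mmol/L in step 2 is illustrative.

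**1. The plan's own figure.** f = (0.3/0.86)/2 = 0.174, in line with the stated 0.175. For the interaction, λ = f²·N·m/(1−ρ), with df1 = (3−1)(3−1) = 4 and df2 = (N−3)(3−1). At N = 69, m = 3 and ρ = 0.5, λ = 0.030625 × 69 × 3/0.5 = 12.68, df2 = 132 and power is 81.1%. At N = 66 power is 79.0%. So 69 reproduces, and the 5% level belongs to the interaction test.

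**2. Within-group reading, no RS effect, same fall in every arm.** The SD of a change from baseline is 0.86 × √(2(1−0.5)) = 0.86.

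| | n = 23 per arm | n = 30 per arm |
|---|---|---|
| SE of mean change | 0.86/√23 = 0.179 | 0.86/√30 = 0.157 |
| Fall 0.3 in SE units | 1.67 | 1.91 |
| Chance that one within-arm test is significant | 36% | 46% |
| Chance that at least one of four (two RS arms, two visits) shows a significant fall (simulated) | 77% | 86% |
| Same, for an assumed fall of 0.15 (simulated) | 37% | 43% |

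**3. Between-group contrasts, no RS effect.** There are four: each RS arm against Control, at each visit. Four independent 5% tests would give 1 − 0.95⁴ = 18.5%. These four are correlated. The shared Control gives 0.5 between arms. With equal correlation ρ between all visits, two changes from the same baseline also correlate at (1−ρ)/(2(1−ρ)) = 0.5, whatever ρ is. Simulated trials (100,000 per setting, n = 23 and 30, ρ 0.3 to 0.7):

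| Rule | Any false result | False benefit |
|---|---|---|
| Interaction test alone | 5% | no direction |
| Four contrasts, no gate | 16.0–16.2% | about 8% |
| Four contrasts, read only after a significant interaction | about 4% | about 2% |
| Four contrasts plus four within-arm RS tests, no gate, no time trend | about 26–27% | about 14% |

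**4. How far the gate protects when one arm works.** With n = 23, ρ = 0.5, RS Supp effective at both visits and RS Diet null, the gated chance of a false RS Diet result is 4.7% in either direction (2.4% for benefit) at the planned 0.3 mmol/L. It is 8.4% (4.2%) at 0.6 mmol/L and 8.9% (4.5%) at 0.86 mmol/L.

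**The case against.** The strongest reply is that the article names one test and powers it. Sample size, the primary outcome section and Statistical analyses all point to the group-by-time interaction, and it holds 5% under the global null. The Background hypothesis is also comparative, against standard dietary advice. The order of contrasts, the choice of adjustment and the handling of follow-up tests after an omnibus result are commonly left to a statistical analysis plan, which is not shown.

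Much of this stands. A reader might infer that the trial runs four separate 5% tests and so has a 16% chance of wrongly declaring RS effective. The documents do not support that. No section states four tests or 5% for each. The 16% also counts results where RS looks worse than Control, which could not be called a reduction; false benefit is about 8% without a gate and about 2% with one. A reader might also infer that the gate fails once RS Supp works. That needs effects of 0.6 to 0.86 mmol/L, beyond the planned 0.3 and the largest cited difference of 0.4. At 0.3 the false RS Diet rate stays below 5%.

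The reply does not reach the wording itself. The article does not leave the primary outcome to a later document. It states it, with the within-group fall on the same footing as the between-group difference. The interaction test does not assess a fall shared by all arms, and it cannot name the arm that the Discussion asks about.

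**Conclusion.** The point holds as a badly fixed primary outcome. It does not show an established false-positive rate of 16%. The within-group reading can be met with no RS effect, in about 77% to 86% of trials if every arm falls by 0.3 mmol/L. That size rests on the assumed common fall, the stated SD of 0.86 and a visit correlation of 0.5; at a fall of 0.15 it is 37% to 43%. The lack of a named arm and visit is a lesser but real gap. It costs between nothing (interaction alone, 5%) and about 16% in either direction (8% for benefit), depending on a reading that the article does not settle. The 0.3 mmol/L criterion shares the defect, since it could refer to change from Baseline or to a difference from Control.

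**What to change.** In the Fasting blood glucose section and in Statistical analyses:

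- Define the primary outcome as the between-group difference in change in FBG, each RS arm versus Control, at one pre-named visit, estimated from the planned mixed model.
- State that the 0.3 mmol/L refers to that difference.
- Control error across the two RS arms by Dunnett or Holm, or by a fixed order stated in advance.
- Label within-group changes, the other visit and RS Supp versus RS Diet as supportive, reported with confidence intervals.

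The sponsor should choose the visit and give the reason, noting that insulin started under the Day 10 rule affects Day 56. Which arm comes first in a fixed order is also the sponsor's choice.

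The cost is wording only, with no extra participants or measurements. Intervals become slightly wider under Dunnett or Holm. Under a fixed order, the second arm cannot be claimed if the first fails. The change should be made before outcome data are seen.

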### Secondary outcomes

#### Post-prandial glucose

Post-prandial blood glucose (PPBG) will be measured by participants using SMBG three times per day for three consecutive days. The change in mean 2-h PPBG and frequency of PPBG levels above the target for each mealtime will be calculated and compared within and between groups at Baseline (Day 1–3), Days 8–10 and Days 54–56. Two-hour PPBG excursions of 6.7 mmol/L or more are considered above the target for optimal pregnancy outcomes [49]. Elevated PPBG are associated with preeclampsia, caesarean section delivery, large for gestational age (LGA), neonatal hypoglycaemia [6] and childhood glucose and IR [10].

#### Time in range for glucose

Participants will be provided with and trained in the use of, a FreeStyle Libre Pro glucose sensor. On Day 1 and Day 42, using aseptic technique and following the manufacturer’s procedure, one FreeStyle Libre Pro glucose sensor (Abbott Diabetes Care, California, USA) will be applied to the mid-triceps area of each participant using a spring-loaded application device supplied with the sensor. A fine, flexible, 5 mm cannula extends from the sensor into the interstitial fluid and the sensor is secured on the skin via an attached adhesive pad. The sensors can be worn in the shower, whilst swimming or exercising. The sensors will be electronically paired with a FreeStyle Libre Pro reader through which the glucose data can be downloaded. The sensors continuously provide interstitial fluid glucose data every 15 min for 14 days and will allow for more accurate assessment of FBG, 2-h PPBG, frequency of 2-h PPBG levels elevated to ≥6.7 mmol/L and time in range (TIR) of optimal blood glucose levels of 3.5–7.8 mmol/L [51]. FreeStyle Libre glucose sensors have been validated in pregnancy against SMBG and found to be safe, accurate and acceptable to users [52]. Ethics approval has been obtained for use of FreeStyle Libre sensors in this study, however, funding for this is to be secured.

#### Requirement for insulin treatment

Data from the participants’ DMR will determine the percentage of women requiring insulin to control blood glucose levels at Day 10 and Day 56 compared to the control group. Participants who require insulin will remain in the study and all samples will be collected. The commencement of insulin to manage glycaemia requires more health care monitoring and intervention, adding burden to the woman and the health care system [18].

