Gut microbiota and glycaemic control are known to be altered by fermentable dietary fibres such as resistant starch (RS) [28, 29, 37, 38]. A systematic review by Colantonio, Werner and Brown [29] concluded that foods with prebiotic properties, such as RS, may improve glycaemic control in women with T2DM. More specifically, a meta-analysis of RS supplementation by Wang et al. [28] showed improvements in fasting glucose and IR, particularly in overweight or obese people with diabetes. Microbial fermentation of RS increases the production of short chain fatty acids (SCFA) [39]. SCFA are thought to improve glycaemic control through multiple mechanisms [20], discussed later, suggesting that the manipulation of the microbiome using RS may be a novel therapeutic option for reducing the severity of GDM.

This study will evaluate whether a high dietary RS intake from diagnosis with GDM can improve maternal glycaemic control; impacts the maternal and/or neonatal gut microbiota, faecal SCFA production, maternal and neonatal health outcomes; and collect information to determine the health economic benefits of improvement of dyads health outcomes that result from this intervention.

We hypothesise that compared with standard GDM dietary advice, women with a high dietary intake of RS from the diagnosis of GDM will show a reduction in fasting blood glucose (FBG) levels and other measures of glycaemic control. This will reduce the percentage of women who require insulin and improve maternal and foetal outcomes.

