### Study population

Participants will be women who are newly diagnosed with GDM and plan to deliver their baby at a tertiary hospital in Western Australia, where all study visits and routine antenatal care will be undertaken. Inclusion criteria include women diagnosed with GDM through a routine 75 g Oral Glucose Tolerance Test (OGTT) between 24 and 30 weeks of pregnancy and ≥ 18 years of age. A diagnosis of GDM is made using the International Association of Diabetes in Pregnancy Study Groups (IADPSG) diagnostic criteria of one or more values reaching the following levels – Fasting glucose ≥5.1 mmol/L, 1-h ≥ 10.0 mmol/L, 2-h ≥ 8.5 mmol/L [41].

Participants will be excluded if they have an early diagnosis of GDM before 24 weeks; Overt Diabetes in Pregnancy; Type 1 Diabetes; T2DM; poorly controlled hypothyroidism; Graves’ Disease; twin pregnancy; breastfeeding; vegetarian; vegan; irritable bowel syndrome; inflammatory bowel disease; previous bariatric surgery; history of an eating disorder; allergy to adhesives; antibiotic use in the past 3 months; use of steroids, antipsychotics, metformin, laxatives, fibre supplements or probiotic supplement; any major medical disorder; any psychosocial issues likely to impact on ability to adhere to study protocol.

Demographic information will be collected from the digital medical record (DMR) and participants will complete a demographic questionnaire at Baseline to obtain information on ethnicity, medical and obstetric history, medication and dietary supplement usage.

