### Intervention

#### Dietary intervention

All women will receive standard GDM dietary advice in line with evidence-based guidelines [2, 40, 43, 44]. Women will be encouraged to consume a minimum carbohydrate intake of 175 g per day, from mostly low glycaemic sources, distributed across the day over three meals and three snacks. The dietary advice will promote a low saturated fat intake and higher consumption of vegetables, fruit, dairy and whole grains.

After Baseline data are collected, women who are randomised to either of the two dietary intervention groups (RS Diet & RS Supp) will receive additional dietary education on consuming a high RS diet commencing on Day 3. All RS dietary education will be conducted by the PI who is an experienced Accredited Practising Dietitian (APD). A standardised teaching plan (Supplement 3) and education materials will be utilised (Supplements 4 & 5). Participants will be provided with written material including a Gut Feeling cookbook [45] and sample menus, as well as some non-perishable samples of high RS foods to allow for immediate adoption of the diet. Dietary RS will be measured at Baseline, Day 10 and Day 56 using 3-day weighed food records (Supplement 6). Evidence of compliance with the high RS diet will also be monitored via urine samples for metabolomic analysis and change in stool microbiota at the same timepoints. Participants will be asked to continue the high RS diet until the delivery of their child.

The RS education tools and strategies have been piloted in a non-pregnant population and achieved a median increase in dietary RS intake of ≥6.6 g RS per day (unpublished data). The typical intake of RS in Australian women aged 19–44 years has been estimated to range from 2.9–8.3 g per day [46]. Similarly, recent data from the United States estimated the mean daily intake of RS to be 1.9 g per 1000 kcal for women of this age [47], which would equate to 3.8–5.7 g per day.

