#### RS supplement

The RS Supp group will consume an RS supplement of high-amylose maize (HAMS) type 2 resistant starch. Participants will be given a 600 g tub of HAMS each fortnight, along with a 40 ml scoop. They will be instructed and provided with written material (Supplement 7) on how to prepare and incorporate the RS supplement into cool fluids or foods in their diet. As with all low-digestible carbohydrates, gastrointestinal (GI) discomfort is a known side effect of rapid introduction of RS, therefore, participants will introduce HAMS over a two-day adjustment period. They will be instructed to consume 1 scoop (20 g) per day for 2 days, taking half in the morning and the rest at night. Then, increasing to a dose of 1 scoop (20 g) morning and night for the remainder of their pregnancy. The RS supplement contains 40% RS type 2. The final amount of RS in the 40 g of HAMS per day will be 16 g, which is below the level of 45 g per day of RS supplementation that is known to be tolerated with minimal side effects, most of which are flatulence [48]. Intakes of up to 80 g RS per day have been tolerated without diarrhoea [48]. Those in the high RS diet plus RS supplement are unlikely to achieve this amount. Consumption and compliance of the RS supplement will be monitored by weight of unconsumed HAMS returned fortnightly. Participants will use a daily RS supplement diary to record intake as an additional measure of compliance. We have shown in a recent 2-week feasibility study, 100% compliance with consumption of the RS supplement and minimal GI side effects in 10 female participants with prediabetes or T2DM (unpublished). GI tolerance of the supplement will be measured via a daily bowel symptom diary for the first 10 days and Days 47 to 56.

Participants can withdraw from the study at any time for any reason. Participants will be withdrawn by the investigator if they commence antibiotics, steroids, metformin or if they can no longer comply with the study’s schedule of assessments (Table 1).

**Table 1 Tab1:** Participant measurements and collection summary

	Day 1	Day 3	Day 10	Day 28	Day 42	Day 56	Day 7 post-partum
Recruitment & consent	√						
Randomisation of subjects	√						
Attend clinic	√	√	√		√	√	
Self-monitoring blood glucose data collection		√	√			√	
FreeStyle Libre Pro application	√				√		
Questionnaires:							
medical Hx	√						
medication	√						
GI symptoms	√		√			√	
Quality of Life SF36	√		√			√	
Weight measured	√		√			√	

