#### Maternal and neonatal outcomes and cost of antenatal care

Maternal and neonatal outcomes data will be collected from the DMR after discharge. Diagnosis Related Group (DRG) [74] data will be collected for calculation of hospital costs. Maternal outcome data collection will include the number of ANC clinic visits, Maternal Foetal Assessment Unit visits, antenatal admissions, delivery method, post-partum maternal length of stay, and feeding method on discharge.

After discharge, data on admission to the Neonatal Intensive Care Unit (NICU), reason for admission and length of stay will be collected from the DMR of the infant to determine the frequency of admissions to NICU in the intervention groups compared to the control group. NICU admission for neonatal hypoglycaemia or respiratory support is a known complication in babies of GDM mothers and is one of our secondary outcomes for the study. There is a linear relationship between glycaemia and admissions to NICU in offspring of women with GDM [6]. We will record this outcome and collect neonatal samples as and when the baby’s clinical condition allows. We accept that research on pregnant women raises particular safety concerns. It is noteworthy that our intervention is safe and we do not expect serious adverse events as a direct result of the intervention. We expect neonatal deaths to be not different from the general population.

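### The insulin outcome stops at Day 56 while the intervention runs to delivery, so insulin starts in late pregnancy are not counted

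*Protocol article*

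**What the plan says.** Under Requirement for insulin treatment, the article takes insulin use from the digital medical record (DMR) and reports "the percentage of women requiring insulin to control blood glucose levels at Day 10 and Day 56 compared to the control group".

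Three places set the length of the intervention, and all run past Day 56:
- Overview of study design: "The dietary intervention will continue until delivery".
- Dietary intervention: "Participants will be asked to continue the high RS diet until the delivery of their child".
- RS supplement: the full supplement regime is kept up "for the remainder of their pregnancy".

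The hypothesis at the end of the Background reads "This will reduce the percentage of women who require insulin and improve maternal and foetal outcomes". It names no date by which the need for insulin is to be judged.

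Entry is set in Overview of study design: "Participants will enter the trial at diagnosis with GDM between 24 and 30 weeks of gestation". The same section places Day 56 at roughly 36 weeks.

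A later look at the record is already planned: "Maternal and neonatal outcomes data will be collected from the DMR after discharge". The items listed there, and in the medical-record rows of Table 1, cover matters such as visits, admissions, delivery, feeding, birth size and NICU care. Insulin use and insulin start date are not among them.

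**The concern.** The question the trial asks is whether women on a high resistant starch intake need insulin less often. The outcome answers a narrower one: whether they are on insulin at two study dates, the later of which can fall weeks before birth. A woman who first needs insulin after Day 56 appears in the outcome only as not on insulin.

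The cut-off is also fixed in study days rather than gestation. The share of treated pregnancy it covers therefore depends on how early a woman entered. At the other end of the entry window, a woman may give birth before Day 56 and then has no status to record at that point.

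What is at stake is the meaning of a secondary result. If the intervention postpones insulin rather than preventing it, a count ending at Day 56 cannot show the difference. The article presents the intervention's value as managing gestational diabetes without medication, so that distinction matters to readers.

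**Working it through.** No figure is stated for the insulin outcome, and the sample size was set for fasting glucose, so it does not bear on this point. The check is date arithmetic.

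**Inputs from the article**
- Entry at 24 to 30 weeks (Overview of study design; the diagnosis window in Study population agrees). One sentence in the Overview gives a wider range, up to 36 weeks, for the Baseline measurements. I use 24 to 30, which the Abstract also gives for Baseline.
- Last insulin count at Day 56, taken as 8 weeks after entry.
- End of intervention: delivery.

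**Assumption, not in the article**
- Delivery at 37 to 40 weeks.

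**The article's own figure.** Day 56 at about 36 weeks is reproduced for entry at 28 weeks: 28 + 8 = 36. Over the whole entry window, Day 56 runs from 24 + 8 = 32 weeks to 30 + 8 = 38 weeks.

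**Formulas**
- Weeks after the last count = delivery week − (entry week + 8), or 0 if negative.
- Share of the entry-to-delivery period = weeks after the last count ÷ (delivery week − entry week).

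| Entry (weeks) | Day 56 (weeks) | Delivery at 37 | Delivery at 40 |
|---|---|---|---|
| 24 | 32 | 5 of 13 (38%) | 8 of 16 (50%) |
| 26 | 34 | 3 of 11 (27%) | 6 of 14 (43%) |
| 28 | 36 | 1 of 9 (11%) | 4 of 12 (33%) |
| 30 | 38 | 0 of 7 (0%) | 2 of 10 (20%) |

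The zero in the last row is not full coverage. A woman who enters at 30 weeks and delivers at 37 gives birth about a week before her Day 56 (38 weeks), so the second count does not exist for her.

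**What the two counts do capture.** A woman who starts insulin between Day 10 and Day 56 and is still on it at Day 56 is counted. The loss is therefore confined to starts after Day 56 and to women who deliver before it.

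**Sensitivity of the percentage.** One reclassified woman moves an arm by 1/30 = 3.3 points at the planned 30 per group, or 1/23 = 4.3 points at the 23 per group left after attrition. This shows how coarse the outcome is. It is not an estimate of how many starts are missed, because the article gives no distribution of insulin start times.

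**The case against.** The strongest reply is that this is a clear definition and not an error. Day 10 and Day 56 are the post-baseline, pre-delivery assessments for fasting glucose, diet, stool and weight, so reading insulin status on the same dates links it to those data. Treatment often continues past the last efficacy assessment, and a hypothesis without a time limit is not contradicted by an outcome that has one. The article also has insulin start when the fasting target is not reached by Day 10, which brings some starts into the observed window. The gap is short for entry near 28 weeks. The outcome is secondary, and the article claims power only for fasting glucose and microbial change. Finally, the list of items reviewed after discharge may not be exhaustive, and extraction fields are often left to a fuller document.

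Most of this limits the weight of the point and stands. It does not remove the point. The two time points are a stated rule, not a detail left for later, and adding a to-delivery count gives up none of the linkage to visit data.

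Three stronger readings are tempting, and the article does not support them:
- *The comparison is biased.* The same cut-off applies to every arm, and randomisation should give similar entry gestation, so the cut-off alone does not favour any group.
- *Delayed starts would be presented as insulin avoided.* The outcome carries its dates in its definition. A report that keeps those dates makes no such claim, and nothing in the article says they would be dropped.
- *The cost analysis inherits the error.* Statistical analyses bases savings on diagnosis-related group codes, activity units and a national price. It does not tie them to the Day 56 percentage, and the group data are described alongside the record collection after discharge.

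**Conclusion.** The point holds as a limited but real weakness in a secondary outcome. The insulin outcome covers less time than the intervention and less than the hypothesis. On the assumed delivery range of 37 to 40 weeks, 0 to 8 weeks of treated pregnancy (0% to 50%) fall after the last count. The upper end needs both the earliest entry and the latest delivery. For entry near 28 weeks, which matches the article's own placing of Day 56, the gap is 1 to 4 weeks (11% to 33%).

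These are weeks of pregnancy, not missed events. The number of uncounted insulin starts could be small and cannot be worked out from the article. The consequence is lost events and an outcome that cannot tell prevention from postponement beyond Day 56. It is worth changing because the better definition answers the trial's own question at very little cost.

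**What to change.** Define the main insulin outcome as any insulin started from randomisation to delivery, with the start date, taken from the DMR. Report cumulative incidence by arm. Keep the percentages at Day 10 and Day 56 as descriptive counts alongside the other measurements at those visits.

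This also gives a defined outcome to a woman who delivers before Day 56. It changes only how insulin use is ascertained and reported. The clinical rule for starting insulin is not touched.

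The cost is a change of wording and one extra field in the record review that is already planned after discharge. No visits, samples or participants are added, and the sample size does not change.
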